**6.0 STUDY PRODUCT/INTERVENTION(S)**

**6.1 Regimen**

Study staff will review the administration of 1% tenofovir gel or matched placebo gel with each participant at her Enrollment Visit. At the Enrollment Visit, the participant will insert one dose of 1% tenofovir gel or matched placebo gel vaginally to a depth of approximately 6 cm under the guidance of the study clinician. Subsequent applications will be inserted daily at bedtime by the volunteers for a dosing total of 14 days. The participant will be instructed on proper insertion technique and storage requirements (see Appendix III).

**6.2 Study Product Formulation and Preparation**

Tenofovir gel is a clear, transparent, viscous gel packaged in epoxy inner-lined aluminum tubes with a white polyethylene screw cap equipped with a puncture tip. Each tube contains six grams of 1% tenofovir gel (w/w) formulated in purified water with edetate disodium, citric acid, glycerin, methylparaben, propylparaben, hydroxyethylcellulose, and pH adjusted to four to five. The gel is applied with a polyethylene applicator capable of administering a four-gram (equal to four ml) dose of gel.

Product should be stored at controlled room temperature until required for administration. Controlled room temperature is defined as 25 degrees Celsius (°C)/ 77 degrees Fahrenheit (°F). Excursions are permitted to 15°C to 30°C (59°F to 86°F).

The placebo for this study is the carrier vehicle gel, which is identical to tenofovir gel without the tenofovir component. The placebo gel will be blinded to the participant, unlabeled and supplied in identically packaged tubes with applicators as the tenofovir gel.

Placebo gel must be stored at controlled room temperature at all times. Controlled room temperature is defined as 25 degrees Celsius (°C)/ 77 degrees Fahrenheit (°F). Excursions are permitted to 15°C to 30°C (59°F to 86°F).

**6.3 Study Product Supply, Packaging and Accountability**

The current Investigational New Drug application (IND) for tenofovir gel is held by DAIDS. Tenofovir gel, placebo and applicators for this study will be provided by Gilead Sciences, Inc. Gilead will manufacture tenofovir gel and placebo gel under good manufacturing practice conditions.

Study gel (active or placebo) will be packaged in cartons containing 16 gel tubes and 16 individually wrapped plastic applicators. A removable portion of the study gel carton will contain unblinded information regarding the identity of the study gel. The AECOM Research Pharmacist will remove all unblinded information and record it appropriately, according to instructions in the NIAID Pharmacy Guidelines.

The pharmacist will maintain an accurate inventory and accountability record of study products received and subsequently dispensed. After the study is completed (or otherwise terminated), all unused study product will be shipped to Gilead Sciences, Inc. for destruction. Participants will be dispensed sixteen (16) single-application tubes of investigational product at the Enrollment Visit. All product, used and unused, will be returned by the participants to MMC/AECOM. The subjects will be counseled that they are to apply 14 daily doses of drug or placebo. They will be instructed that they will be given 2 extra doses of drug or placebo to use only if a dose is dropped or lost.

6.4 Assessment of Participant Adherence with Study Product/Intervention(s)

The first application of investigational product will be done at the enrollment visit by the participant under the guidance of the study clinician. Participants will be instructed to apply the assigned investigational product once daily at bedtime for 13 subsequent days (see Appendix III).

Participants will be asked to record information on the number of times they administer study gel, time of each insertion, and emergence/resolution of specific symptoms in a study diary. Diaries will be reviewed at each visit.

Non-adherence will be defined as three or more days (out of 14) of missed product use. Participants who miss less than three days will (if practical according to their expected date of menses onset) be asked to apply product for additional days to attempt to achieve a full 14 days of product exposure. An additional participant will be recruited for each non-adherent participant. Participants who are non-adherent with the study protocol will be asked their reasons for non-adherence and this information will be recorded on the applicable study forms. Study procedures for Day 3, Day 7, Day 14, and the Final Visit will be re-scheduled as necessary. Participants will be instructed to call the study staff in the event of missed doses to re-schedule study visits.

Participants will be instructed to abstain from sexual relations throughout the course of the study. If a participant is found to have engaged in anal or vaginal sexual relations or experienced vaginal penetration with anything other than the study gel applicator throughout the study, this information will be recorded on applicable case report forms.

A participant with a clinical toxicity outcome (see Appendix IV) who is discontinued from further product use will be considered to have reached a study endpoint and will not be replaced. Standard clinical care will be provided and followed to resolution.

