**9.6 Criteria for Permanent Treatment Discontinuation for an Individual Participant**

The criteria for permanent treatment discontinuation of further study product/intervention(s) for an individual participant are:

- Treatment-related toxicity (see section 9), including pelvic inflammatory disease, deep epithelial disruption
- Requirement for prohibited concomitant medications such as oral antibiotics
- Pregnancy or breastfeeding
- Completion of treatment as defined in the protocol
- Request by participant to terminate treatment
- Clinical reasons believed life-threatening by the physician even if not addressed in the toxicity section of the protocol
- Unwillingness or inability to remain abstinent for the duration of the study.

The participant will continue to be followed with participant’s permission if study product/intervention (s) is discontinued.

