**9.7 Criteria for Premature Study Discontinuation for an Individual Participant**

The criteria for premature discontinuation from the study for an individual participant are:

- Participant repeatedly non-compliant with study treatment as prescribed (missing more than three doses of study product throughout the 14 days of product use)
- Pregnancy or breastfeeding
- Request by participant to withdraw
- Request of the primary care provider if s/he thinks the study is no longer in the best interest of the participant
- Participant judged by the investigator to be at significant risk of failing to comply with the provisions of the protocol as to cause harm to self or seriously interfere with the validity of study results
- At the discretion of the IRB, Food and Drug Administration, NIH, investigator, or pharmaceutical supporter.

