## 10.0 STATISTICAL CONSIDERATIONS

## 10.1 Overview and Statistical Designs Issues

## All subjects who receive treatment (1% tenofovir gel or matched placebo gel) will be included in all analyses. The primary objective of this study is to assess the mucosal response to repeated applications of 1% tenofovir gel or matched placebo gel by examining cervicovaginal secretions for cytokines chemokines, defensins, SLPI and lactoferrin as well as changes in the cell population in CVL pellets. A secondary objective is to assess whether the intrinsic antimicrobial (HSV, *E. coli* and *Staph aureus*) activity of CVL is altered following 14 days of daily intravaginal use of 1% tenofovir gel or matched placebo gel and correlate any observed changes in antimicrobial activity with changes in levels of mediators of mucosal immunity. An exploratory objective is to measure and compare the levels of tenofovir detected in serum and CVL.

The outcome is the level of individual proteins obtained after application of drug compared with placebo gel or total number of white blood cells and of specific cell types in CVL pellets. Differences between groups with respect to age and baseline amounts of mediators will be compared by *t* test. Differences between groups with respect to change in cytokines, chemokines, mediators of mucosal immunity, cell numbers, and antimicrobial activity will be compared by analysis of covariance and adjusted for baseline (after log transformation of data for cytokines, chemokines, and mucosal mediators). Differences between groups with respect to change in fold reduction in viral or bacterial infection after application of drug or placebo gel relative to titers in screening CVL samples will be determined by Wilcoxon nonparametric test (with exact p-values) on log transformed data. Calculations will be done using SAS software (version 9; SAS Institute).

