**13.5 Study Discontinuation**

Once a participant has enrolled in the study, the study site will make every reasonable effort to retain her for the complete study period. Given the relatively small study sample size, and the importance of ascertaining all outcomes among study participants, 100 percent retention of enrolled participants is targeted.

However, participants may withdraw from the study for any reason at any time. The Principal Investigator (PI) also may withdraw participants from the study in order to protect their safety and/or if they are unwilling or unable to comply with required study procedures.

During the study, participants with any abnormal condition will be treated according to standard clinical practice. A participant with a clinical toxicity outcome (see Appendix IV) who is discontinued from further product use will be considered to have reached a study endpoint. Participants also may be withdrawn if the study sponsor or regulatory authorities terminate the study prior to its planned end date.

Every reasonable effort will be made to complete a final evaluation of participants who terminate from the study prior to completion, and study staff will record the reason(s) for all withdrawals from the study in participants’ study records.

If at the screening or enrollment visits, a participant is found to have an abnormality on pelvic exam or a urinary tract infection, she will be ineligible to enroll in the study. Following treatment for candida vaginitis, bacterial vaginosis or urinary tract infection, she may be eligible to be re-screened for participation in the study. A minimum interval of one month is required between treatment and re-screening and all exclusion criteria will apply. If a participant is found to be pregnant, she will be referred for care.

Accrual into this study will be suspended if two or more participants experience similar grade 3 or higher AEs (as defined by the DAIDS Table for Grading Severity of Adverse Experiences) judged possibly, probably, or definitely related to product use. The protocol team in collaboration with the Safety Committee and NIH Medical Officer then will review all pertinent data and determine whether to continue accrual and product use. The team may decide to stop the study at this time, or at any such time that the team agrees that an unacceptable type and/or frequency of AEs have been observed.

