## Appendix IV: Outcomes, Diagnostics, and Follow-Up Procedures

Individual participants may withdraw from study participation at any time, for any reason, without loss of other benefits or services to which they may be entitled. Participants with any abnormal condition will be treated according to standard clinical practice.

| **Condition** | **Product Use** | **Evaluation** | | **Enrollment Action** | | **Follow-up and Treatment Action** | |
| --- | --- | --- | --- | --- | --- | --- | --- |
| Ulceration | Adverse clinical event, discontinue product use | Culture for genital herpes. |  | | Re-evaluate in 5 to 7 days. If the ulcer has become worse or not healed in 5 to 7 days, perform a biopsy. Ask the participant to return in 7 to 10 days for follow-up. | |  |
| Abrasion | Continue |  |  | | Re-evaluate by speculum examination in 48 to 72 hours. If the condition is worse, discontinue product use. If the condition is the same, continue product use. | |  |
| Generalized erythema or severe edema: A localized area of more than 30% of vulvar surface or combined vaginal and cervical surface affected by erythema | Adverse clinical event, discontinue product use |  |  | | Re-evaluate in 5 to 7 days. | |  |
| Vaginitis | Adverse clinical event, discontinue product use | Perform wet mount for *candida vaginitis, trichomoniasis,* and bacterial vaginosis. |  | | Manage with oral medication and re-evaluate in seven days. If resolved, restart product use. If the participant has asymptomatic candida vaginitis at the Day 7 visit she should continue product use and be re-evaluated at the Day 14 visit.[[1]](#footnote-2) | |  |

| Suspected cervicitis | Provisionally continue | Evaluate for *N. gonorrhoeae and C. trachomatis*. Perform wet mount for  *trichomoniasis.* | If laboratory results confirm pathogen, discontinue treatment. | Treat with oral medication and re-evaluate in 5 to 7 days. |
| --- | --- | --- | --- | --- |
| Petechial hemorrhage | Continue |  |  | Re-evaluate by speculum examination in 48 to 72 hours. If the condition is worse, discontinue product use. If the condition is the same, continue product use. |
| Ecchymosis | Continue |  |  | Re-evaluate by speculum examination in 48 to 72 hours. If the condition is worse, discontinue product use. If the condition is the same, continue product use. |

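### Section 9.7 ends study participation for missed doses, so lavage samples from treated women may be lost although Section 10.1 counts every treated woman in every analysis

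*Protocol*

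**What the plan says.** Four parts of the protocol bear on a treated woman who misses doses.

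- **Section 6.4** sets the definition: "Non-adherence will be defined as three or more days (out of 14) of missed product use". It adds: "An additional participant will be recruited for each non-adherent participant". A woman taken off product for a clinical toxicity outcome is handled differently: she "will be considered to have reached a study endpoint and will not be replaced".
- **Section 9.7** lists grounds for ending a woman's participation in the study. One is repeated non-compliance, specified as "missing more than three doses of study product throughout the 14 days of product use".
- **Section 9.6** covers women who stop product only. Here "The participant will continue to be followed with" her permission.
- **Section 10.1** defines the analysis population: "All subjects who receive treatment (1% tenofovir gel or matched placebo gel) will be included in all analyses".

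Sections 10.4 and 13.5 both set complete retention as the target, because the sample is small and all outcomes need to be ascertained. For those who leave early, 13.5 adds: "Every reasonable effort will be made to complete a final evaluation of participants who terminate from the study prior to completion".

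Appendix IV directs that product be stopped for vaginitis, and then: "Manage with oral medication and re-evaluate in seven days. If resolved, restart product use".

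**The concern.** The primary objective (Section 3.1) is the mucosal response to 14 daily applications, read from CVL. The Day 14 sample is therefore central, and Day 21 shows whether a change persists after dosing ends. A rule that ends study participation because doses were missed can stop those samples being taken. If an analysis plan exists, it can choose how to handle the gap but cannot recover the samples.

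The gap may not be random. Section 2.4 reports genital pruritus in 23% of participants in the earlier Phase I study of this gel, and one woman who stopped after 10 days with vulvar ulcerations judged probably related to product. The diary described in Section 4.0 collects symptoms and reasons for non-adherence. Section 2.1 justifies the whole study by mucosal changes that clinical examination may miss. Women who skip doses because the gel irritates them are thus a foreseeable group, and their lavages would be informative.

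**Working it through.** **1. The rules side by side.** Dosing is once daily, so missed days in 6.4 and missed doses in 9.7 count on the same scale.

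| Missed of 14 | Section 6.4 | Section 9.7 | Section 10.1 |
|---|---|---|---|
| 0 to 2 | adherent; missed days made up if practical | stays | analysed |
| exactly 3 | non-adherent; one extra woman recruited | stays | analysed |
| 4 or more | non-adherent; one extra woman recruited | discontinued from study | analysed, but later visits no longer scheduled |

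The two cut-offs disagree only at exactly three, and that woman stays in the study with her data. Data can be lost only in the last row.

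**2. Which samples are exposed.** CVL after first dosing is scheduled on Days 3, 7, 14 and 21. The first dose is supervised on Day 0 and home dosing starts the next night, so four missed doses can accumulate by Day 4 at the earliest. If they are found at the Day 7 visit, the Day 14 and Day 21 samples are exposed. If the fourth is found at the Day 14 visit, where a lavage is already scheduled, only Day 21 is. Section 13.5 asks for one final evaluation, without naming CVL or a day. At best it could stand in for one of the two.

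**3. The plan's own sample-size figure.** Inputs from Section 10.2: difference δ = 0.55 log, SD σ = 0.5 log, n = 12 per arm, two-sided α = 0.05, stated power 80%.

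Normal approximation: power = Φ(δ / (σ√(2/n)) − 1.96). Here σ√(2/12) = 0.204 and 0.55/0.204 = 2.694, so power = Φ(0.734) = 76.9%. The noncentral t with 22 degrees of freedom gives 73.1%. With the baseline-adjusted analysis of Section 10.1, the SD shrinks by √(1 − ρ²). At an assumed baseline correlation ρ = 0.4, power is 80.0% (76.8% at 0.3, 84.3% at 0.5); the protocol gives no correlation. The stated figure is therefore attainable under adjustment. None of this depends on the adherence rules.

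**4. What the rules do to power.** The protocol gives no non-adherence rate, so the counts below are assumptions. Unadjusted, δ = 0.55, σ = 0.5:

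| Analysed per arm | Situation | Normal | t test |
|---|---|---|---|
| 12 | none lost, or one lost and one recruited | 76.9% | 73.1% |
| 13 | one non-adherent woman kept, plus one recruited | 80.1% | 76.8% |
| 11 | one lost, none recruited | 73.2% | 69.0% |
| 10 | two lost, none recruited | 69.1% | 64.3% |

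Every woman withdrawn for missed doses (four or more) is also non-adherent under 6.4 (three or more), so each triggers a recruit. The first two rows follow the protocol; the last two contradict 6.4.

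**5. Balance.** If added women shifted a total of 24 to 13:11, the equivalent equal-arm size would be 2/(1/13 + 1/11) = 11.9 per arm, which is negligible.

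**6. Directed holds.** A hold of seven days for vaginitis exceeds three missed days. The no-replacement sentence in 6.4 covers women discontinued from further product use. Whether it reaches a woman who restarts is not stated, nor is whether her hold days count as missed use.

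**The case against.** The best defence is that the protocol uses different cut-offs for different actions, which is untidy but not contradictory: one triggers recruitment and the other ends participation. Section 10.1 keeps every treated woman, 6.4 speaks of an additional participant rather than a substitute, and visits may be re-scheduled after missed doses. Samples already collected are kept, and 13.5 seeks a final evaluation. Much of this stands, and it rules out several stronger readings that a reader might infer.

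- **That the one-dose mismatch loses data.** It does not; the woman at exactly three remains in the study and the analysis.
- **That Day 14 and Day 21 lavages are never taken.** Too strong, given 13.5 and the lavage already scheduled at Day 14.
- **That power falls to about 64%.** That needs two women lost per arm and none recruited, which 6.4 excludes.
- **That results are biased toward no effect.** The protocol links missed doses to no mediator level. Keeping under-dosed women can itself dilute an effect of 14 daily applications.
- **That a woman on a directed hold is withdrawn as non-compliant.** Section 9.7 concerns compliance with treatment as prescribed, and a woman who stops on instruction is complying. The open question lies in 6.4.
- **That same-arm replacement would break the blind.** The Research Pharmacy provides the randomisation and its pharmacist handles the unblinded carton information (6.3, 10.3), so study staff need not learn the allocation.

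What the defence does not answer is the last row of the first table. A woman with four or more missed doses leaves the study by rule, while 10.1 promises that she is in every analysis.

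**Conclusion.** The concern holds in a limited form. Sections 9.7 and 10.1 do not fit together: 9.7 can stop the collection of later CVL samples from treated women whom 10.1 analyses and whom 10.4 and 13.5 aim to retain. Section 9.6 shows that follow-up off product is already acceptable in this trial, so ending it for missed doses is not forced by the design.

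Each affected woman is 1/12 = 8.3% of an arm, and up to two of her four post-dosing lavages are exposed if the fourth missed dose is found at Day 7. That missed doses relate to irritation is plausible from the protocol's own background, but it is an assumption. The number of such women, and the size and direction of any bias, cannot be derived from the protocol. No loss of power follows as long as the extra women are recruited. The matter is worth correcting because the remedy is cheap and samples not taken cannot be recovered, not because a distortion has been shown.

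**What to change.** 1. In 9.7, state that missed doses alone do not end follow-up. Scheduled CVL visits continue with the participant's permission, as 9.6 already provides for women who stop product. Decisions about product use are not touched.
2. In 6.4 and 10.1, state that women recruited for non-adherence supplement the non-adherent women and do not substitute for them. The non-adherent women are analysed as randomised. State how added women are randomised.
3. Reconcile the missed-use thresholds in 6.4 and 9.7. Which cut-off is right is not judged here.
4. Reconcile 6.4 with Appendix IV on whether days on an investigator-directed hold count as missed product use, and whether a woman who restarts falls under the no-replacement sentence. The answer is for the protocol team.

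The cost is a few sentences and the completion, for a few non-adherent women, of visits already scheduled. Under-dosed women may slightly dilute an effect, and the analysed number may exceed 24 and not be exactly 12:12.

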## 6.5 Concomitant Medications

Enrolled participants may continue use of all concomitant medications except vaginal products(lubricants, feminine hygiene products, and vaginal drying agents) during this study. All concomitant medications (including complementary and alternative medicines, vitamins, etc.) will be recorded on applicable study case report forms. Medications used for the treatment of AEs that occur during study participation also will be recorded on applicable case report forms.

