# 5.2 Exclusion Criteria

Women who meet any of the following criteria (by self-report, unless otherwise specified, at screening, enrollment, or at anytime during participation, unless otherwise specified) will be excluded from this study:

- Are pregnant (based on a urine pregnancy test) or less than 6 months post-partum.
- Are currently breastfeeding.
- Are menopausal.
- Are currently using hormonal contraception or have used hormonal contraception in the previous 2 months.
- Are currently menstruating (at screening or enrollment visits – may be eligible for deferment).
- Have a positive HIV test at screening.
- Have a positive urine culture at screening (may be eligible for re-screening after treatment).
- Have a positive chlamydia, gonorrhea, or trichomonas result at screening.
- Have an abnormal Pap smear (if documentation of a negative result within the past year is not available).
- Have a clinically detectable genital abnormality (i.e., vulvar, vaginal, cervical and/or perianal ulcer and/or lesion or an abnormal wet mount).
- Have a history of Toxic Shock Syndrome, or a history of symptoms suggestive of Toxic Shock Syndrome.
- Have a history of intermenstrual bleeding in the 3 months prior to enrollment.
- Have had gynecological surgery or received treatment for syphilis, genital herpes, chlamydia, gonorrhea, trichomonas, or genital warts in the last 6 months.
- Have received treatment for candida, bacterial vaginosis, or urinary tract infection in the prior month.
- Have douched or used any vaginal products**,** including lubricants, feminine hygiene products, vaginal drying agents and sex toys during the 48 hours prior to enrollment.
- Have had sexual intercourse during the 48 hours prior to enrollment.
- Have evidence of acute or chronic hepatitis B infection (defined as + HBV core IgM, + HBV core IgG or + HBsAg).
- Have evidence of liver or kidney abnormalities (defined as ALT or AST >2x normal, Total bilirubin >1.2 mg/dl, and creatinine >1.2 mg/dl).
- Oral antibiotics in the past 7 days.

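### Sections 6.5, 5.2, 9.6 and Appendix IV give conflicting rules on oral antibiotics during the study, and section 10.1 keeps lavage taken on such drugs in the antimicrobial endpoints

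*Protocol*

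**What the plan says.** Section 6.5 sets the on-study medication rule: "Enrolled participants may continue use of all concomitant medications except vaginal products". For drugs given to treat adverse events it adds only a recording duty: "Medications used for the treatment of AEs that occur during study participation also will be recorded on applicable case report forms".

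Section 9.6 lists, among the reasons for permanently stopping product, "Requirement for prohibited concomitant medications such as oral antibiotics". It then says that the participant "will continue to be followed with participant’s permission if study product/intervention (s) is discontinued".

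Section 5.2 lists "Oral antibiotics in the past 7 days" as an exclusion. The header of that list applies its items at screening, at enrollment and at any later time in the study unless an item says otherwise, and this item does not.

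Appendix IV, which section 9.1 makes the guide for continuing or holding gel, names oral medication in two rows:
- Vaginitis: gel is stopped, then "Manage with oral medication and re-evaluate in seven days. If resolved, restart product use".
- Suspected cervicitis: "Treat with oral medication and re-evaluate in 5 to 7 days", with gel provisionally continued and stopped if the laboratory confirms a pathogen.

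Section 10.1 fixes the analysis set: "All subjects who receive treatment (1% tenofovir gel or matched placebo gel) will be included in all analyses". Lavage is collected at every visit (section 4.0), and the anti-viral and anti-bacterial assays are listed for each visit in section 7.1.

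**The concern.** Two things are at stake.

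The first is conduct. Section 9.6 refers to prohibited medications, but section 6.5, where a reader looks for the prohibition, bars only vaginal products. Appendix IV prescribes oral treatment together with a restart or continuation of gel. If the oral drug is an antibiotic, staff can follow the protocol and still do different things with the same woman. In a trial of 12 per arm whose question is the effect of 14 daily doses, that makes exposure depend on interpretation.

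The second is the functional endpoint. The secondary objective asks whether the secretions' own activity against HSV, *E. coli* and *S. aureus* changes. A woman treated with a systemic antibacterial or antiherpes drug goes on giving lavage, and section 10.1 counts it. Any active drug in that lavage could not be told apart from host activity.

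**Working it through.** **Step 1. The rules side by side, for a woman given an oral antibiotic on study.**

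| Section | Status of the drug | Gel | Follow-up |
|---|---|---|---|
| 6.5 | allowed | no restriction | drug recorded |
| 5.2 with its header | exclusion | not addressed separately | excluded from the study |
| 9.6 | prohibited | stopped permanently | continues with permission |
| Appendix IV, vaginitis | oral medication given, class not named | stopped, restarted if resolved | continues |
| Appendix IV, suspected cervicitis | oral medication given, class not named | provisionally continued; stopped if a pathogen is confirmed | continues |

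Appendix IV does not say that its oral medication is an antibiotic. Appendix V, however, gives a course of oral antibiotics as an example of treatment for Grade 2 cervicitis, and antibiotics or antifungals for Grade 2 vulvovaginitis. The protocol therefore foresees the case in which the rules collide.

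**Step 2. What this does to exposure.** Section 4.0 targets the Day 7 visit after 7 doses and the Day 14 visit after 14.
- Suspected cervicitis treated with an oral antibiotic at Day 7, no pathogen confirmed: section 9.6 ends exposure at 7 doses; Appendix IV and section 6.5 allow all 14.
- Vaginitis so treated at Day 7: re-evaluation falls on Day 7 + 7 = Day 14, with 7 doses taken on either reading. They part afterwards. Under section 9.6 the Day 21 lavage comes about 21 − 7 = 14 days after gel was stopped. Under Appendix IV it may come after a restart. This assumes visits are not rescheduled, which section 6.4 permits.

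**Step 3. Whether lavage can coincide with treatment.** For suspected cervicitis treated at Day 7, re-evaluation falls on Day 7 + 5 = 12 to Day 7 + 7 = 14. The Day 14 lavage window is Days 12 to 15 (section 4.0). Course lengths are not given, so overlap is plausible but not established.

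The bacterial control in section 4.1 carries the same penicillin and streptomycin that the laboratory adds to lavage. It does not offset a drug the participant is taking.

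**Step 4. Possible size.** The only planning figures are in section 10.2: 12 per arm, SD about 0.5 log for most immune mediators, a difference of about 0.55 log, 80% power, two-sided 0.05. Check by the normal approximation: 0.55 / (0.5 × √(2/12)) − 1.96 = 2.69 − 1.96 = 0.73, which is 76.9% power, and 13 per arm for 80%. An SD of 0.48 gives 80.1%, so rounding of the approximate inputs can explain the gap. The present point does not rest on this; it only borrows the SD.

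Assume that SD for the antimicrobial assays, no true gel effect, and k women in one arm only whose samples gain d log from a drug. The mean shift in that arm is k × d / 12. Rejection rates at nominal 5%, from 4,000 simulated trials (Monte Carlo standard error about √(0.05 × 0.95 / 4,000) = 0.3 percentage points):

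| k | Mean shift at d = 0.5, 1, 2 log | Exact Wilcoxon | t test |
|---|---|---|---|
| 0 | 0 | 4.6% | 5.4% |
| 1 | 0.04, 0.08, 0.17 | 4.5%, 4.2%, 4.0% | 4.8%, 4.6%, 4.0% |
| 2 | 0.08, 0.17, 0.33 | 5.5%, 6.4%, 7.4% | 6.0%, 7.8%, 9.3% |
| 3 | 0.13, 0.25, 0.50 | 6.8%, 9.8%, 11.5% | 7.8%, 12.8%, 19.5% |

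Both columns are relevant because section 10.1 names antimicrobial activity under analysis of covariance and the fold reduction under the exact Wilcoxon test. The t test is a rough stand-in for the former, without the baseline covariate.

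**The case against.** A reader might infer more: that the plan scores rescue drug as intrinsic activity and so biases the gel comparison toward reassurance. The documents do not support that.
- Only two Appendix IV rows name oral medication. The rows for abrasion, erythema or edema, petechiae, ecchymosis and sub-epithelial hemorrhage name no drug. The ulceration row names a herpes culture but no antiviral; treatment there rests on a general sentence about standard practice. So rescue is not clearly tied to gel injury.
- No document names a drug, its activity against the three test organisms or its level in lavage. Secretions are washed in 10 ml of buffer and diluted again in the assays.
- No treatment rate is given, and the women are healthy, abstinent and screened negative for gonorrhea and chlamydia.
- One affected woman hardly moves the Wilcoxon test.

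All of that stands, and it limits the second part of the point to a possibility.

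It can also be said that the antibiotic item in section 5.2 reads naturally as an entry criterion. That is fair, but the header does not confine it to entry, and sections 6.5, 9.6 and Appendix IV conflict without it.

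Finally, handling of intercurrent medication commonly belongs in an SAP, which is not shown, so its absence from the protocol is no fault. What the protocol does state, in section 10.1, is that these women stay in every analysis.

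**Conclusion.** The contradiction is established on the text. Sections 6.5, 5.2, 9.6 and Appendix IV cannot all be followed when the oral drug is an antibiotic, and the difference can be 7 doses against 14 for one woman. No SAP can repair it, because it governs what happens at the site.

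The effect on the functional endpoints is possible and of unknown size. It requires a drug active against a test organism to reach the lavage in more than one woman, mostly in one arm. Under the assumed SD of 0.5 log and shifts of 0.5 to 2 log, two or three such women in one arm raise the Wilcoxon rejection rate to between 5.5% and 11.5%; one does not raise it.

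Two further inferences are not supported. One is that on-treatment samples should leave the main analysis: with 12 per arm, that would be a post-randomization exclusion related to outcome and could create the bias it aims to avoid. The other is that systemic corticosteroids need an entry exclusion by analogy with hormonal contraception. Section 2.2 bases that restriction on the expected low use of hormonal methods in developing countries, not only on mediator levels.

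**What to change.** 1. Reconcile sections 6.5, 5.2 and 9.6 and Appendix IV into one consistent rule on oral antibiotics and other systemic antimicrobials during the study, covering product use and continued participation. Which rule stands is for the investigators to decide.
2. Keep the all-treated analysis in section 10.1 as primary. Flag lavage samples taken during systemic antibacterial or antiviral use, from the concomitant-medication data that section 6.5 already requires, and add a sensitivity analysis of the HSV, *E. coli* and *S. aureus* endpoints without the flagged samples. If an SAP already does this, only the first change is needed.

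No new sampling instruction is called for: section 7.1 already lists lavage within the speculum exam, ahead of the referral to Appendix IV. The cost is amendment wording, one data flag and one extra analysis.
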